#### **Telephone Calls Days 3, 7, and 14**

Volunteers will also be telephoned on Days 3 (+/- 1 day), 7 (+/- 2 days), and 14 (+/- 2 days), to inquire about adverse events and discuss study drug use. A standardized form that asks the same questions that are listed in the diary (Appendix C) will be developed for this purpose. Open-ended questions will also be asked to solicit adverse events. The volunteer will be reminded to call the PI or study staff at any time to discuss any questions or changes in health status.

### **7.3 Follow-up (Day 28 (End of Treatment), Day 56 (End of Study))**

Study subjects will return for follow-up evaluations to the clinical study site on study day 28 and 56. The following evaluations and procedures will occur at each visit.

- Interval medical history, concomitant therapy/medications, consumption of probiotics, yogurt, etc and adverse event questionnaire, self report and diary review
- Physical exam with weight and vital signs
- Routine Laboratory tests
  - CBC

- Serum chemistries/liver function tests
- Research Laboratory tests
  - Collection of nasopharyngeal specimens for microbiota
  - Collection of stool sample for microbiota and LGG culture
  - Sub-study only – blood for DNA, mRNA and cytokines
- Study drug cultures for colony counts (day 28 only)

At the follow-up visits, subjects will be reminded to contact the PI at any time for any issues or adverse events that occur. On day 28, subjects will receive a new stool container and again be instructed on how to collect the stool.

## 7.4 Early Termination Visit

Subjects are free to withdraw from participating in the study at any time upon request. The reason for withdrawal will be documented on the CRF. If a subject withdraws early due to an adverse event, he/she will be followed until resolution/stabilization of the adverse event. Subjects will be withdrawn if they are hospitalized.

If a subject prematurely withdraws from the study or is withdrawn from the study, the same procedures and evaluations will be performed as in the final study visit if possible at the time of withdrawal from the study (i.e. study subject withdraws at time of a visit and consents to having procedures/evaluations done):

- Interval medical history, concomitant therapy/medications, consumption of probiotics, yogurt, etc and adverse event questionnaire, self report and diary review
- Physical exam with weight and vital signs
- Routine Laboratory tests
  - CBC
  - Serum chemistries/liver function tests
- Research Laboratory tests
  - Collection of nasopharyngeal specimens for microbiota
  - Collection of stool sample for microbiota and LGG culture
  - Sub-study only – blood for DNA, mRNA and cytokines

## **8 STUDY PROCEDURES/EVALUATIONS**

[name] and her study team are responsible for ensuring that all study procedures and evaluations are performed.

### **8.1 Clinical Evaluations**

- Medical history from subject interviews
  - Medical history, current conditions, review of symptoms
  - Drug allergies
  - Concomitant medications
- Physical examination
  - Vital signs, height, weight
  - Exam of body systems – HEENT, neck, heart, lungs, abdomen, skin, musculoskeletal, neurologic, lymph nodes, vascular, other

### **8.2 Laboratory Evaluations**

#### **8.2.1 Clinical Laboratory Evaluations**

The following clinical laboratory evaluations will be performed by the Tufts Medical Center or Massachusetts General Hospital CLIA-approved clinical laboratories.

- Hepatitis panel and HIV (screening) - HCV antibody, HBsAg, HIV antibody.
- Drug and alcohol toxicity screen
- CBC – hemoglobin, WBC with differential, platelet count.
- Serum chemistries/liver function tests – alkaline phosphatase, AST, ALT, total bilirubin, BUN, creatinine, glucose.

#### **8.2.2 Special Assays or Procedures**

##### **8.2.2.1 Culture of LGG**

All cultures for LGG will be processed and performed in [name] research laboratory at Tufts Medical Center using standard culture methods.

### 8.2.2.2 Microbiota

All samples for microbiota will be processed in preparation for bacterial RNA/DNA extraction by homogenizing the specimen with RNALater (Qiagen, Valencia CA) and then stored at – 80 C in multiple microfuge tubes. The batched samples will have purified bacterial DNA/RNA extracted and will be amplified using PCR. The PCR products will be pooled and pyrosequenced. Our current procedures are as follows, although these may be modified at the time that the batched analyses are run, due to likely scientific advances. Homogenates of stool will be thawed, and DNA will be extracted using a ZYMO Fecal DNA Kit (Zymo Research, CA). The purified DNA will be stored at - 80°C in the tissue bank for future batched pyrosequencing of 16S rRNA genes at the University of Maryland's Institute of Genomic Sciences (IGS). Purified DNA, labeled only with study ID, specimen type and visit identifier, will be subjected to PCR to generate amplicons of 16S rRNA genes for pyrosequencing by protocols established by IGS. The forward primer for all stool DNA samples will be the 16S rRNA gene primer 454\_27F

(GCCTTGCCAGCCCGCTCAGTCAGAGTTTGATCCTGGCTCAG, Sigma-Aldrich, Inc, St. Louis MO) . The reverse primer for each sample will be constructed to contain a unique tag sequence to serve as a "barcode" to identify its origin. After amplification, the PCR products will be pooled and pyrosequenced at IGS on a Roche/Life Sciences 454 Pyrosequencer (Branford, CT). To evaluate possible contamination of reagents and subsequent amplification of foreign DNA during PCR amplification, control reactions that contain reagents but no DNA template will be included in each PCR run. If this negative control shows positive amplification, the PCR will be repeated with fresh reagents. To limit contamination, all DNA handling will be performed in a dedicated hood, barrier tips will be used on pipettes to avoid cross-contamination, and gloves will be changed regularly. To help control for PCR-induced biases , quantitative PCR will be used to find the amplification saturation point for each sample. During the PCR amplification, the minimum number of cycles will be used to reach the amount of DNA product needed for pyrosequencing. The procedures for the nasopharyngeal samples are the same except that DNA will be extracted using the DNA Mini Kit (Qiagen, Valencia, CA). Samples are only identified with a study ID number, specimen type and study visit descriptor.

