#### **11.3.2 Microbiota Richness and Diversity**

Richness will be reported as the number of operational taxonomic units. Diversity will be reported as the Shannon Diversity Index. Additional graphical output such as heat maps will be generated.

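### The only negative control enters at the PCR step, so bacterial DNA introduced at collection, preservation or extraction would go undetected and be counted in nasopharyngeal richness

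*Protocol*

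**What the plan says.** Protocol section 8.2.2.2 (Microbiota) sets the order of work: specimens are homogenised in RNALater and frozen, DNA is extracted with a kit and stored, and the DNA is later amplified, pooled and sequenced.

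- **Negative control.** In the amplification stage, "control reactions that contain reagents but no DNA template will be included in each PCR run". If it is positive, the response is: "If this negative control shows positive amplification, the PCR will be repeated with fresh reagents".
- **Preventive measures.** "To limit contamination, all DNA handling will be performed in a dedicated hood, barrier tips will be used on pipettes to avoid cross-contamination", together with regular glove changes.
- **Amplification.** For each sample, "quantitative PCR will be used to find the amplification saturation point for each sample", and "the minimum number of cycles will be used to reach the amount of DNA product needed for pyrosequencing".
- **Nasopharyngeal samples.** "The procedures for the nasopharyngeal samples are the same except that DNA will be extracted using the DNA Mini Kit". No further control is added for them.

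Section 11.3.2 then says: "Richness will be reported as the number of operational taxonomic units". Diversity is the Shannon index. No step for removing contaminants is stated. Under section 3.2.2, richness and diversity at both body sites are secondary outcomes, and the Time and Event Schedule places sampling at Days 0, 28 and 56.

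**The concern.** A no-template reaction contains only PCR reagents. It can reveal foreign DNA in those reagents, but DNA that came in with the collection device, the preservative or the extraction kit is already part of the template, and that template is exactly what the control leaves out. The control could therefore stay negative while extracts carry contaminant DNA.

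Richness is a plain count, so a contaminant taxon adds as much as a resident one. A fixed number of extra OTUs would raise the level but cancel in a within-subject comparison. The number detected is not fixed, however: it depends on how much specimen DNA competes with the contaminant DNA for reads. A change in bacterial load from one visit to the next can then resemble a change in the community. The study has one treated group and no concurrent control. Section 2.1.9 says that no nasopharyngeal microbiome data exist in elderly subjects, so there is also no reference against which an implausible taxon would stand out.

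**Working it through.** The documents give no figure on this point, so there is none to reproduce. The check is a reading of the workflow followed by an illustration on assumed inputs.

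**1. Where DNA can enter and what is checked** (section 8.2.2.2)

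| Step | Possible source | Negative control named? |
|---|---|---|
| Collection | device or tube | no |
| Preservation | RNALater | no |
| Extraction | kit (one for stool, another for nasopharyngeal) | no |
| PCR | PCR reagents | yes, in each run |

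The remedy matches the control: fresh PCR reagents deal with the last row only.

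**2. Number of samples.** 10 to 15 subjects × 3 visits × 2 sites = 60 to 90 samples, of which 30 to 45 are nasopharyngeal.

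**3. How many contaminant OTUs would be counted.** All inputs here are assumptions. Let C be contaminant and B specimen 16S copies per extract, K = 20 equally abundant contaminant OTUs, and N reads per sample.

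- Contaminant share: s = C / (B + C)
- Expected contaminant OTUs seen: K × [1 − (1 − s/K)^N]

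Example: C = 100, B = 10,000, N = 1,000. Then s = 100/10,100 = 0.0099, and 20 × [1 − (1 − 0.0099/20)^1000] = 7.81.

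| B | C = 100, N = 1,000 | C = 100, N = 5,000 | C = 1,000, N = 1,000 | C = 1,000, N = 5,000 |
|---|---|---|---|---|
| 10^3 | 19.79 | 20.00 | 20.00 | 20.00 |
| 10^4 | 7.81 | 18.32 | 19.79 | 20.00 |
| 10^5 | 0.97 | 4.42 | 7.81 | 18.32 |
| 10^6 | 0.10 | 0.49 | 0.97 | 4.42 |
| 10^8 | 0.00 | 0.00 | 0.01 | 0.05 |

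**4. Change between visits.** Suppose load falls tenfold with no change in the resident community. With C = 100 and N = 1,000, a fall from 10^5 to 10^4 adds 7.81 − 0.97 = 6.84 OTUs. With C = 100 and N = 5,000, the same fall adds 18.32 − 4.42 = 13.90. With C = 1,000 and N = 5,000, a fall from 10^4 to 10^3 adds 20.00 − 20.00 = 0. The artefact can thus be nil or substantial, depending on where the specimens lie. The calculation ignores resident OTUs lost when contaminants take up reads. No figure is given for the Shannon index, because it also depends on the resident community's own diversity, which the documents do not state.

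**5. Does cycling to a target amount make it worse?** After c cycles at equal efficiency the share is C·2^c / (B·2^c + C·2^c) = s. For C = 100 and B = 1,000 it is 9.09% after both 20 and 35 cycles. The cycle rule leaves the share unchanged; it means only that the final product amount does not show that an extract was poor in specimen DNA.

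**The case against.** The strongest reply has four parts.

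**The procedure is not final.** Section 8.2.2.2 calls these the current procedures, allows them to change when the batch is run, and leaves amplification to the sequencing centre's protocols. Contaminant filtering could sit there or in a statistical analysis plan that is not at hand. This stands in part: one can say only that contaminant OTUs would be counted unless removed. But a filter needs a blank to work from, and a blank has to be prepared when the extraction is done. Neither an analysis plan nor a downstream PCR protocol can supply it afterwards, and leave to modify is not a commitment to add one.

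**There are other contamination measures.** A reader might take the PCR control to be the only protection. It is not: the hood, barrier tips and glove changes cover DNA handling. They reduce handling contamination, but they neither detect nor remove DNA already present in a reagent or device.

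**Low biomass is not documented.** A reader might infer that these are sparse swab specimens. Sections 7.2, 7.3 and 8.2.2.2 speak only of nasopharyngeal specimens or samples and give no device or load. This stands, and it is why the size cannot be fixed.

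**The low-template signal is not lost.** A reader might conclude that the cycle rule worsens the contamination or erases the sign of a poor extract. Neither follows. The share does not change, and the per-sample quantitative PCR still carries information on starting template. What is missing is a rule for using it.

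**Conclusion.** The point holds as a gap in the laboratory controls. The one negative control and its remedy cover PCR reagents only, and the richness definition has no stated filter, so contaminant DNA entering before PCR would be undetected and would add to the OTU count unless removed.

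Its size cannot be taken from the documents. Under the assumptions above, between none and all of 20 contaminant OTUs would be counted. At 10^8 specimen copies the expected number is at most 0.05, so stool is probably little affected if its load is of that order.

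Two stronger conclusions are not supported. The first is a percentage inflation of richness: any such figure would come wholly from assumed counts, and it would describe the level at one visit, not change between visits. The second is that the trial would wrongly credit LGG with a microbiota effect: sections 3.1 and 11.3.2 plan description only, with no test or decision rule. The consequence is confined to a descriptive secondary outcome, and the primary safety outcome is untouched. This is a worthwhile, cheap improvement.

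**What to change.** In section 8.2.2.2:

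- Carry at least one blank per extraction batch and kit (an unused collection device or tube plus RNALater) through extraction, PCR and sequencing under its own barcode.
- Use the per-sample quantitative PCR already planned, run on the blank as well, to flag specimens whose signal does not exceed the blank.
- Extract all visits of a subject in the same batch.

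In section 11.3.2, remove OTUs that the blanks identify as contaminants before computing richness and the Shannon index, and report both measures with and without this removal.

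The cost is a few extra libraries. Two kits are named, so one batch per kit means 2 blanks and two batches per kit means 4, against 60 to 90 study samples; batch sizes are not stated. There is also a filtering step in the analysis. The drawback is that a few true low-abundance taxa shared with the blank may be removed, which reporting both versions would make visible. No procedure is added for subjects.

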### 8.2.2.3 Immune Response Genes

DNA and RNA will be extracted from blood using the Paxgene kits and will be stored for future analysis of immune response genes and immune response gene products such as cytokines as follows. The subject's RNA will be extracted from 5 mL of whole blood per visit. The RNA will be stored at -80 C for later batched analysis of RNA gene expression profiles in [name] laboratory at the USDA-ARS in Beltsville, Maryland. Its quality and quantity will be analyzed by the Experion automated electrophoresis system (Biorad) and equal RNA amounts (10 micrograms) per each sample will be used for first strand cDNA synthesis using Superscript II Reverse Transcriptase (Invitrogen) . Cytokine production in response to bacterial stimulation will be analyzed using real time PCR by following the kinetics of mRNA expression of pro-inflammatory cytokine genes (i.e. TNF- $\alpha$ , IL-12, IL-6, IFN $\gamma$ ), anti-inflammatory genes (IL-10) and different signaling pathways (i.e. Mitogen activated protein kinase (MAPK) p38, phosphatidylinositol 3 (PI3) kinase, and nuclear

factor Kappa B (NF-KB) involved in probiotic-induced cytokine production as previously described in vitro. Two grams of stool per visit will also be stored at -80 C and provided to [name] to enable her to extract bacterial DNA from the specimens. Samples are only identified with a study ID number, specimen type and study visit descriptor.

## 9 ASSESSMENT OF SAFETY

### 9.1 Subject Evaluations

Study staff will inquire about symptoms (anticipated adverse events) using standardized and opened ended questions and at each study visit. AEs will also be solicited during telephone calls on study day 3, 7, and 14. In addition, routine physical examinations and safety labs will be assessed at all study visits.

Subjects will also be asked to keep a daily symptom diary. Subjects will be instructed on how to complete this diary at the baseline visit. Subjects will document all symptoms experienced and the intensity of the symptoms on a daily basis. The symptom diary will be reviewed at all study visits. The diary will also be reviewed during scheduled telephone calls on Days 3 (+/- 1 day), 7 (+/- 2 days) and 14 (+/- 2 days). A phone script will be utilized for this purpose during these scheduled calls. If any symptoms have been recorded in the diary and are reported during the scheduled telephone call, a study physician will follow-up with the subject by phone. The study physician will then determine how to rate the event based on his/her evaluation and will arrange for appropriate follow-up and treatment, if necessary. An additional study visit may be scheduled. The study physician will complete the appropriate AE form for all adverse events identified during the scheduled phone calls and study visits, as well as during any unscheduled calls or visits.

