| Stool culture for LGG – if positive, PFGE/PCR compared to administered LGG |                                | X                 | X                        | X                      |
| Stool and nasopharyngeal samples for microbiota                            |                                | X                 | X                        | X                      |
| Study drug colony counts                                                   |                                | X                 | X                        |                        |
| Sub-study blood (DNA, RNA, cytokines)                                      |                                | X                 | X                        | X                      |
| Adverse events – questionnaire, self report and subject diary              |                                | X                 | X                        | X                      |

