### **7.2 Enrollment (Baseline Visit, Day 0)**

Subjects who are eligible to participate in the study after all of the screening tests have been completed will return for a baseline visit. The following evaluations and procedures will be done at the baseline visit, prior to receiving the study drug:

- Interval medical history, concomitant therapy/medications, consumption of probiotics, yogurt, etc and review of symptoms

- Physical exam with weight and vital signs
- Routine Laboratory tests
  - CBC
  - Serum chemistries/liver function tests
- Breathalyzer - Alcohol screen
- Research Laboratory tests
  - Collection of nasopharyngeal specimens for microbiota
  - Collection of stool sample for microbiota and LGG culture

Enrolled subjects will be offered an opportunity to participate in the sub-study. After they either decline or accept, study drug will be dispensed.

- Study drug cultures for colony counts
- First administration of study drug. Subject will learn how to take the study drug twice daily for the next 4 weeks.
- Sub-study only – blood for DNA, mRNA and cytokines

Subjects will be reminded to contact the PI at any time for any study related issues or adverse events that occur. Subjects will receive a new stool container and again be instructed on how to collect the stool.

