### 9.4 Adverse Events

#### 9.4.1 Definitions

An **adverse event (AE)** is any undesirable experience associated with the use of a medical product in a subject (<http://www.fda.gov/medWatch/report/DESK/advevnt.htm>). An AE can therefore be any

unfavorable and unintended sign (including an abnormal laboratory finding), symptom, or disease temporally associated with the use of a study drug. Study subjects will be monitored for the occurrence of events from the day of enrollment for a maximum period of 2 months, although intense monitoring of adverse events will occur during the first 28 days when the subject is taking LGG. The occurrence of an AE may come to the attention of study staff during study visits and interviews with a study subject presenting for medical care, or upon review by a study monitor. In addition, subjects will be evaluated in person or by telephone and asked about unanticipated adverse events. We will use both open-ended questions and specific questions about possible adverse effects, such as presence of diarrhea and other abdominal symptoms.

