## 9.6 Rescue Medication

There is a theoretical risk of translocation of LGG across the bowel wall and resultant clinical infection caused by *Lactobacillus*. Possible infections include bacteremia, endocarditis, or abscesses. The antibiotic susceptibilities of LGG, as reported by various researchers, are attached (Appendix C). Based on the available literature, including experimental models of infective endocarditis with *Lactobacillus plantarum*, we would recommend treatment of *Lactobacillus* endocarditis with a beta-lactam and gentamicin, but bacteremia alone or other sites of infection may be treatable with a beta lactam only. If any study subject develops invasive disease

(bacteremia, endocarditis, etc.), we will recommend this treatment course, but will also ask that an independent infectious disease physician (not involved in the study) evaluate and treat the subject. We will also obtain *in vitro* sensitivity data on the specific isolate as several articles show a benefit of treating with antibiotics to which the organism is sensitive *in vitro*.

The dose, route, frequency, and duration of treatment will be determined by the infectious disease consultant caring for the subject but the recommended regimens are as follows:

Ampicillin 2 grams intravenously every 6 hours (or alternative beta-lactam antibiotic) for 14 days  
or  
Clindamycin 900 mg intravenously every 8 hours for 14 days or  
Moxifloxacin 400 mg intravenously every 24 hours for 14 days

Alternative oral regimens for these 3 drugs should the subject be able to transition to an oral regimen to complete the 14 days of therapy are as follows:

Ampicillin 500 mg orally every 6 hours (or alternative beta-lactam antibiotic) for 14 days or  
Clindamycin 300 mg orally every 8 hours for 14 days or  
Moxifloxacin 400 mg orally once a day for 14 days

At the conclusion of therapy for invasive disease, we will obtain throat and stool cultures to determine whether the subject is colonized with LGG in either of these locations. The *in vitro* susceptibility pattern of the isolate will be rechecked to guide additional antibiotic therapy to eradicate the LGG. Subjects will be followed until LGG is no longer isolated from these potential colonizing sites.

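### The diary and the call form copied from it do not name fever, chills, headache, fatigue or myalgia, and 'new' symptoms are judged against a baseline taken without that daily instrument

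*Protocol*

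**What the plan says.** Section 9.1 sets up the diary. It states that "Subjects will document all symptoms experienced and the intensity of the symptoms on a daily basis" and that "Subjects will be instructed on how to complete this diary at the baseline visit". Appendix C prints the rows: bloating, gas, intestinal rumbling, diarrhea, blood in stool, abdominal cramps or pain, nausea, vomiting, loss of appetite, abnormal taste, heartburn, constipation and skin rash, followed by three blank 'Other' lines.

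For the calls at Days 3, 7 and 14, section 7.2 says: "A standardized form that asks the same questions that are listed in the diary (Appendix C) will be developed for this purpose". It adds: "Open-ended questions will also be asked to solicit adverse events". Section 9.4.1 also promises specific questions, and its only example is "such as presence of diarrhea and other abdominal symptoms".

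Before dosing on Day 0, section 7.2 lists an interval history that includes "consumption of probiotics, yogurt, etc and review of symptoms". The Time and Event Schedule row "Adverse events – questionnaire, self report and subject diary" is marked at Baseline, Day 28 and Day 56, but not at Screening.

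The primary outcome (section 3.2.1) is a new Grade II-IV toxicity possibly or probably related to LGG. Section 4 treats new as not present at baseline and gives no look-back period. On the infection risk, section 9.6 says: "Possible infections include bacteremia, endocarditis, or abscesses".

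**The concern.** Two weaknesses affect the same primary outcome.

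The first is unequal ascertainment. Gut symptoms are prompted by name every day and on every call, while the general symptoms of systemic infection are not. A subject asked each day about gas but not about feverishness will report gas more completely. Between Day 14 and Day 28, and again between Day 28 and Day 56, no call is scheduled, so the diary is the only scheduled instrument. Fever in Appendix A is graded on a measured oral temperature, but vital signs are scheduled only at visits and the diary does not ask for a temperature.

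The second is the baseline. The trial has a single arm of 10-15 subjects, so a subject's own pre-dose state is the reference for what is new. That state is established by history and a review of symptoms on one day, whereas afterwards symptoms are recorded daily. The two are not measured alike, and the difference favours finding new symptoms on drug. No analysis can later recover pre-dose days or unprompted symptoms that were never recorded.

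**Working it through.** **1. Item lists side by side**

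| Symptom | Named in diary and call form | Graded in Appendix A |
|---|---|---|
| Nausea/vomiting | yes | yes, systemic table |
| Diarrhea | yes | yes, systemic table |
| Headache | no | yes, systemic table |
| Fatigue | no | yes, systemic table |
| Myalgia | no | yes, systemic table |
| Fever | no | yes, vital signs table |
| Chills | no | no row |

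Three of the five systemic rows are not named, and neither is fever. Of the five missing symptoms, four are graded.

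Myalgia was also not settled by the sponsor's pilot. Section 2.1.7.1 gives muscle aches in 0 LGG and 6 placebo subjects, while section 2.1.8.3 says myalgias were significantly more common with LGG.

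**2. How a one-day baseline behaves**

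The protocol gives no event rate or power figure on this point, so there is nothing to reproduce. What follows illustrates the mechanism under assumed rates.

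Suppose a symptom occurs on a fraction p of days regardless of LGG, days are independent, and the baseline sees Day 0 only. The chance that it is absent on Day 0 but present on at least one of 28 treatment days is (1-p)[1-(1-p)^28].

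For symptoms of any grade:
- p = 2%: 0.98 × (1 - 0.98^28) = 42%
- p = 5%: 0.95 × (1 - 0.95^28) = 72%
- p = 10%: 0.90 × (1 - 0.90^28) = 85%

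The outcome needs Grade 2 or higher, so much smaller daily rates are relevant. The values of p below are assumptions. The last columns use 1-(1-q)^n, where q is the per-subject chance.

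| Assumed p | q per subject | At least one case, n = 10 | n = 15 |
|---|---|---|---|
| 0.1% | 2.8% | 24% | 34% |
| 0.5% | 13% | 75% | 88% |
| 1% | 24% | 94% | 98% |

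These figures are for one symptom and come before any judgement of relatedness. The spread is so wide that it sets no size for the actual outcome.

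**3. What a 7-day look-back would change**

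If seven symptom-free days are required, and all are recalled, the first factor becomes (1-p)^7. The chances for p = 2%, 5% and 10% fall from 42%, 72% and 85% to 38%, 53% and 45%. For p = 0.5% the change is only from 13.0% to 12.6%. A look-back therefore helps with frequent intermittent symptoms and does little for rare ones.

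**The case against.** The strongest reply is that the protocol has other routes to these symptoms. Subjects are told to record everything they experience, there are three write-in lines, and calls and visits include open questions. Vital signs, examination and blood counts are done at Days 28 and 56, and an investigator can be reached at all hours. The visit questionnaire is separate from the diary and its items are not shown. This stands. A reader might infer that infection symptoms are not asked about at all. The protocol does not support that; they are only not prompted by name in the diary and call form.

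The baseline is also more than a Day 0 tick-list. A medical history is taken at screening and an interval history on Day 0. Section 5.3 excludes diarrhea, constipation or vomiting lasting more than 12 hours in the preceding four weeks. Study physicians rate reported symptoms and can call them not related or remote. This too stands, and it means background symptoms do not automatically become primary outcome events. It does not close the gap. Short episodes of gas or bloating fall outside that exclusion, and 'possible' in section 9.4.2.2 requires a reasonable time sequence while allowing the subject's clinical state as a cause.

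A reader might also take the pilot's 17/21 (81%) placebo event rate as the background rate here. It counts any event, in subjects aged 18-49, after LAIV, which Stage I does not give.

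Finally, the gut-focused list has a rationale. Section 2.1.7.1 classes headache, muscle aches, weakness and chills as possibly related to LAIV, and Appendix A says its tables do not require every parameter to be monitored. So the omission breaches no rule. It remains a weak choice when section 9.6 names invasive infection as the theoretical risk.

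**Conclusion.** The concern holds in a limited form. Between visits, five systemic symptoms are not solicited by name, four of which the protocol's own scale grades, and the scheduled instruments are thereby tilted towards gut complaints. Separately, 'new' is judged against a baseline that did not use the daily instrument applied afterwards, so intermittent symptoms can be misclassified as new.

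The first part rests on the printed lists and needs no assumption. The second is a real mechanism whose size for related Grade 2 or higher events cannot be derived from the documents. The 42%, 72% and 85% figures might be read as the expected contamination of the primary outcome. They should not be: they apply to any grade, assume independent days and a Day 0-only baseline, and ignore relatedness. Clustered symptom days would lower them.

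This is a recommended improvement to data collection. It does not invalidate the design.

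**What to change.** Add rows for fever (with measured temperature), chills, headache, fatigue and muscle aches to Appendix C and to the Day 3, 7 and 14 call form.

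At the Day 0 visit, before dosing, go through the same item list with a stated look-back, for example the prior 7 days, and state in section 4 that 'new' is judged against it. Because this does little for rare symptoms, Grade 2 or higher events should still be described individually.

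Optionally, give the diary for Day -7 to Day -1, but only to subjects already found eligible. About 80 people are to be screened for 10-15 enrolled, so issuing it to everyone at screening would burden many who never take part. This option needs screening to be complete at least 7 days before Day 0, which fits the Day -31 to Day -1 window.

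The cost is a form revision, slightly more work for subjects, and a few more nonspecific background symptoms reported, since every added row is another chance to report one.
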